### Trial design

The GET UP trial is designed as a two-arm, randomised controlled trial with two parallel clustered groups assigned to an intervention group (IG) or a control group (CG) stratified by region (Figs. 1, 2 and 3).

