### Assignment of interventions (for controlled trials)

#### Allocation

The randomisation is stratified by region, and by physician’s gender, using a random block randomisation sequence generated in Stata software (version 13, StataCorp, College Station, TX, USA). The GP’s surgery is the unit of randomisation. A GP investigator and their patients will be assigned to the same group. The patients will not know to which group their GP has been randomised. Investigators from the same GP’s surgery are randomised within the same group in order to avoid contamination bias.

The participating GPs will be randomised using Stata version 13 (StataCorp, College Station, TX, USA) which is an online, central randomisation service. Allocation concealment will be ensured as the service will not release the randomisation code until the GP has been recruited into the trial in each region.

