#### Statistical methods

Analyses will be performed using Stata software, version 13 (StataCorp, College Station, TX, USA). All data will be analysed on intention to treat. The tests will be two-sided, with a type I error set at *α* = 0.05. Baseline characteristics (GPs and their patients) will be presented for each randomisation group as the mean ± standard deviation (SD) or the median (interquartile range) according to statistical distribution for continuous data and according to the number of patients and associated percentages for categorical parameters.

The comparisons between the randomised groups will be carried out using the Student *t* test or the Mann-Whitney test where appropriate, (1) normality verified by the Shapiro-Wilk test and (2) homoscedasticity by the Fisher-Snedecor test for quantitative parameters and using chi-squared or Fisher’s exact tests for categorical variables.

Outcomes will pertain to the cluster level using usual statistical tests and with more specific approaches at the individual level. Hierarchical regression models (generalised linear mixed model due to binary endpoint) will be performed as primary analysis: (1) to estimate the effect of intervention on the incidence of new cases of patients suffering from acquired and lifelong PE, natural variable PE and premature-like ejaculatory dysfunction and (2) to take into account the variability between and within, the GP cluster groups. Intra-class correlation coefficients will be presented by arm with a 95% CI. Then, GP characteristics (gender, age, geographical area) or patient characteristics (age, socioeconomic status) should be considered as covariate (fixed effects in mixed models) in adjusted multivariable analyses. The adjusted and unadjusted results will be presented: absolute numbers of patients who have raised the topic of PE with their related GP, relative risks and 95% CIs.

For secondary endpoints, comparisons at the individual level between randomised groups will be performed using an analysis of covariance for correlated data with the baseline score as a covariate, as suggested by Klar and Darlington [31] for the SF-12 quality of life scores. Results will be expressed as effect-sizes and 95% CIs. The PEDT will be analysed as a quantitative score using statistical methods described for the SF-12 quality of life and as a binary outcome (< ≥ 11) with the use of a generalised linear mixed model.

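### Randomisation is stratified by region and GP gender, but the primary mixed model as described contains neither; if they are prognostic, the primary test is somewhat conservative and loses a little power

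*Protocol article*

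**What the plan says.** On the design, the protocol article's Allocation section states: "The randomisation is stratified by region, and by physician’s gender, using a random block randomisation sequence". The Trial design section mentions one factor only, with clusters "assigned to an intervention group (IG) or a control group (CG) stratified by region", and the Abstract likewise refers only to four areas.

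On the analysis, the Statistical methods section states: "Hierarchical regression models (generalised linear mixed model due to binary endpoint) will be performed as primary analysis". It gives that model two purposes: to estimate the intervention effect, and to allow for variability between and within GP clusters. No stratification factor is named there. The next step reads: "Then, GP characteristics (gender, age, geographical area) or patient characteristics (age, socioeconomic status) should be considered as covariate". Gender and geographical area are thus listed beside GP age, patient age and socioeconomic status, none of which was stratified on. The section then adds: "The adjusted and unadjusted results will be presented".

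**The concern.** Stratified randomisation makes the arms more alike on region and GP gender than chance would. The arm difference then varies less from one allocation to another. An analysis that leaves the factors out does not know this: it counts their contribution to between-GP variance as error. If the factors are prognostic, the standard error is too large, the test rejects less often than its nominal 5%, and some of the precision gained by stratifying is lost.

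The plan puts the two design factors in a later, discretionary step, in a list joined by an *or*, so that an adjusted model need not contain either. An analysis plan that followed this text would carry the mismatch forward. What is at stake is precision in the primary comparison, not its validity.

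**Working it through.** **Plan's own figures.** The article gives no figure for the effect of stratification, so there is none to reproduce on this point. As a check on the shared inputs (5% versus 20%, two-sided alpha 0.05, power 90%), the pooled formula gives

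n = [1.96·√(2·0.125·0.875) + 1.2816·√(0.05·0.95 + 0.20·0.80)]² / 0.15² = 100.06, so 101.

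That matches the article's 101, although the formula yields it per arm. That is a separate matter and carries no weight here.

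**Inputs from the article.** 40 GPs, about 15 patients each, four regions, two genders (4 × 2 = 8 strata), ICC 0.05 to 0.20, alpha 0.05 two-sided.

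**Assumptions.** Share of between-GP variance explained by region and gender (R²): 0, 10, 25 or 50%. Block sizes 2 or 4. Each GP randomised singly.

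**Direction.** For cluster means with perfect balance on the strata, true variance of the arm difference divided by the variance the unadjusted test estimates is

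1 − R²·ρ / [ρ + (1 − ρ)/m].

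With ρ = 0.20 and m = 15, ρ/[ρ + (1 − ρ)/m] = 0.20/(0.20 + 0.0533) = 0.79. The ratio is 0.92, 0.80 and 0.61 for R² of 10, 25 and 50%, and 1 when R² = 0. It never exceeds 1, so the error can only be towards conservatism. This is a limiting case: strata of about five GPs leave incomplete blocks and some imbalance, so the simulated effect is milder.

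**Size.** Simulation with region and gender omitted or included as main effects. Between-GP variance was set so that the ICC on the proportion scale is about 0.10 at a 5% rate and 0.20 at a 20% rate. Type I error: 1,500 replicates at 12.5% in both arms. Power: 600 replicates at 5% versus 20%.

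| R² | 0% | 10% | 25% | 50% |
|---|---|---|---|---|
| Cluster-level t test, type I, unadjusted | 0.046 | 0.037 | 0.039 | 0.029 |
| Same, adjusted | 0.053 | 0.043 | 0.055 | 0.053 |
| Cluster-level t test, power, unadjusted | 0.895 | 0.890 | 0.922 | 0.923 |
| Same, adjusted | 0.887 | 0.907 | 0.940 | 0.962 |
| Mixed model (likelihood ratio), type I, unadjusted | 0.061 | 0.048 | 0.049 | 0.030 |
| Same, adjusted | 0.077 | 0.079 | 0.085 | 0.083 |
| Mixed model, power, unadjusted | 0.932 | 0.920 | 0.938 | 0.947 |
| Same, adjusted | 0.942 | 0.943 | 0.970 | 0.987 |

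Monte Carlo standard errors are about √(0.05·0.95/1500) = 0.006 for type I error and √(0.9·0.1/600) = 0.012 for power. Adjusted and unadjusted tests used the same simulated data, so their differences are less noisy than that.

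- **Cluster-level test.** The power gain from adjustment is 1.7, 1.8 and 3.9 points at R² of 10, 25 and 50%. At R² = 0 adjustment costs 0.8 points.
- **Second simulation of cluster means.** 8,000 runs, 12 patients per GP, ICC 0.20, all eight stratum terms fitted. At R² = 0 power was 0.73 unadjusted and 0.71 adjusted, a cost of 2 points.
- **Mixed model.** The unadjusted likelihood-ratio test stays near 5% at R² of 10 to 25%, because its liberality with 40 clusters offsets the conservatism. It falls clearly below 5% only at 50%. The adjusted test runs at about 8%, so part of its apparent power gain is liberality.
- **Smaller between-GP variance** (ICC about 0.04 and 0.09). Power is about 99% either way. The adjusted likelihood-ratio test is still liberal, at 0.065 to 0.076.
- **Smaller true effect** (8% versus 17%, cluster-level test, larger variance). The gap is wider: 0.436 versus 0.458, 0.456 versus 0.508, and 0.399 versus 0.555 at R² of 10, 25 and 50%. The 2 to 4 points therefore apply to the planned effect.

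**The case against.** The strongest reply is that the loss is conditional. No passage says that region or GP gender explains any between-GP variance, and if they explain none, the unadjusted test is correctly sized and adjustment costs a little power. That stands. A reader might infer from the mismatch that the primary p value and interval are too conservative as a matter of fact; the article does not support that.

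The article's primary model is a mixed model, and there the unadjusted test was near nominal at moderate R². That stands too. Simply adding two covariates and keeping an uncorrected likelihood-ratio test would make things worse. So the remedy needs a small-sample method.

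The simulated balance is somewhat idealised. Allocation makes the surgery the unit of randomisation and keeps GPs of one surgery together, so a surgery with GPs of both genders cannot be balanced on gender as cleanly. The effect may therefore be smaller than shown.

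It is also fair that adjusted results, which may include both factors, are already promised, and that a full covariate list can be left to an analysis plan that is not shown. This reduces the point but does not remove it: the article does describe its primary model, and it places the stratification factors outside it.

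A reader might also infer that presenting adjusted and unadjusted results leaves the primary result open to choice. The order of the text argues against that: the mixed model is called primary and adjustment follows it. Presenting both is ordinary reporting. Finally, the Abstract and Trial design do not say that region is the only factor, so that discrepancy is minor.

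**Conclusion.** The point holds as a matter of efficiency. The plan randomises within region and GP gender, but its primary model as described ignores both. If the two factors explain 10 to 50% of between-GP variance (an assumed range), a cluster-level test without them has a type I error of about 3 to 4%, and power about 2 to 4 points below the adjusted test at 5% versus 20%. If they explain nothing, adjusting costs about 1 to 2 points at most. The omission neither biases the effect estimate nor inflates the type I error. Whether the trial has enough patients is a different question and adds nothing to this one. The change is worth making because the likely gain is at least as large as the possible cost, and the variables are already known at randomisation.

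**What to change.** In Statistical methods, state that the single primary test is the arm effect from the generalised linear mixed model with region and GP gender as fixed effects (3 + 1 = 4 parameters) plus the cluster random effect.

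Name a small-sample correction suited to about 40 clusters. Examples are a t reference distribution with between-cluster degrees of freedom, or a cluster-level analysis adjusted for the same two factors. With 40 clusters the cluster-level version has 40 − 6 = 34 degrees of freedom, against 38 unadjusted.

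Label the unadjusted model, and models with further GP or patient covariates, as supportive. In the Abstract and Trial design, name the same stratification factors as in Allocation.

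The cost is a few sentences, four degrees of freedom and slightly more analysis work. No new data are needed.

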**Methods:**

A cluster randomised controlled trial, stratified over four areas comparing an intervention group, which will receive the six strategies training session, and a control group, which ensures routine medical care. The primary outcome is to investigate the efficacy of a training in communication skills directed towards this pathology, compared with usual care procedures, on the incidence of patients bringing up the topic of PE with their GP. The secondary objective relates to the variation in the quality of life of patients after having recently addressed the topic of PE. Quality of life will be evaluated using the SF-12 health scale, with scoring filled in by the patient immediately after the consultation and 4 weeks later. The patients suffering from PE will be identified if their score is higher than 9 on the Premature Ejaculation Diagnostic Tool filled in 4 weeks after the consultation. The number of patients necessary to highlight a significant difference between the two groups from 5 to 20% is 101. Therefore, a total of 600 patients is expected, 300 in each arm (40 GPs, 15 patients per GP; risk *α* = 5%; power = 90%; intra-cluster correlation coefficient *ρ* = 0.2; Hawthorne effect = 15%; lost-to-follow-up rates for GPs = 10% and for patients = 20%).

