## Methods

### Outcome

The primary outcome is the incidence of patients bringing up the topic of PE with their GP.. This was undertaken in the group where the GPs received training in communication skills directed towards this pathology, compared with the patients who received the usual care procedures.

The secondary outcome relates to the variation in the quality of life of patients after they have addressed the topic of PE as measured by the SF-12 questionnaire.

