### Participants, interventions, and outcomes

#### Eligibility criteria

##### Patient inclusion criteria

Consecutive male patients, between 18 and 80 years old, and consulting for a sexual, urogenital or psychological reason will be included. We added age limits to the registered protocol because, above 80 years of age, the specificity of the care required for those of advanced age was out the scope of the study. A list of sexual, urogenital, and psychological reasons extracted from the International Classification of Primary Care, Second edition (ICPC -2) classification will be provided for the GPs to guide their inclusions. The GPs will inform the patient of the study after knowing the reason for the encounter, at the beginning of the consultation. The key information is written on a consent form where the study on sexual dysfunction is described and where it is explicitly written that the patient agrees to participate in the study. The patient will sign the document after he has been given the explanations. The participants will not be incentivised to take part.

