three attitude-related strategies for revealing the problem:Being particularly receptive to the patient throughout the consultation: especially at the end when the physician was about to open the door, in order to create a gap that the patient could use to express his problem. The physician consciously creates an attentive environment, using non-verbal behaviour which will encourage the patient to speak freelyUsing humour: lightening the atmosphere by using gentle humour without being vulgar or insensitiveTaking a matter-of-fact approach to play down any embarrassment in the patient’s view of sexuality: emphasising the natural and mechanical function of sexuality allows the GP to play down the emotional aspect of the subjectThree investigative strategies with interviews deliberately directed towards sexual dysfunction:Systematic questioning during consultations dedicated to preventionSymptoms that the patient could be experiencing: the GP suggests a list of signs and symptoms connected to the current clinical situation, for instance: ‘you’re presenting symptoms of depression, and depression may bring on physical, psychological, and even sexual tiredness’. The patient chooses one of these to talk about his PEFacilitating the patient’s verbal expression, enquiring about the patient’s psycho-social and medical history and his daily environment enables the subject of PE to be raised

The training session will be provided by the Steering Committee member in each of the four regions. Their expertise is as follows: three have had specialised training in sexology and three have had specialised training in education. They will receive audio-visual training in the presentation of the slides to ensure the replication of the intervention. GPs will be trained, with practice situations, using role-play performed with the committee member and the other GPs. Available treatments, based on the ‘guidelines for the diagnosis and treatment of premature ejaculation’ [8] will be presented during the session. The session will end with the presentation of the outcome questionnaires.

The intervention session will follow this agenda:30 min will be devoted to brainstorming1 h to the presentation of theoretical elements, and2 h will be devoted to role-play practice situations

The intervention will occur at the GP’s surgery or during a professional meeting, depending on the choice of the GP.

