#### Data collection

##### Outcomes and measurements

To measure the incidence of patients suffering from acquired and lifelong PE, natural variable PE and premature-like ejaculatory dysfunction, the final diagnosis of PE will be made by referring to the answers given to the Premature Ejaculation Diagnostic Tool (PEDT) sent back by the patient 4 weeks after the consultation (please refer to the ‘Measurements’ section). The patients suffering from PE will be identified if their score is higher than 9 on the PEDT. The PEDT questionnaire is an extensively validated, self-report measure that can systematically assess DSM-IV-TR criteria to provide accurate diagnoses of PE/no-PE [26]. It is a screening tool with cut-off scores, brief and easy to administer, and recommended by the International Society of Sexual Medicine [8, 26, 27]. The self-report questionnaire, in our opinion, seems to handle delicate, intimate questions with appropriate sensitivity. We followed a linguistic and cultural validation procedure to obtain a French version of the questionnaire. Additional file 4 is an abstract describing the procedure we followed.

Patients in the two groups will have to complete a self-report questionnaire on quality of life, the SF-12 questionnaire, in a French-validated version right after the consultation, and again, 4 weeks after the consultation [28]. The SF-12 questionnaire right after the consultation will be available in the waiting room. The SF-12 questionnaire, 4 weeks after the consultation, will be posted or e-mailed to the patient. The SF-12 is a self-report questionnaire exploring quality of life [28]. The original questionnaire contained 36 items divided into eight scales, the SF-36 [28]. The SF-12 was created to shorten the responses and included one or two items from each of the eight SF-36 scales. The French version of the SF-12 is correlated to the SF-36 [28]. We chose a general quality of life self-report questionnaire for several reasons. A generic scale was useful to avoid influencing patients in the CG. The availability of a validated French version was another argument supporting the choice of this scale [28].

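### The SF-12 score called baseline is taken after the consultation in which the intervention acts, so the planned ANCOVA can misstate the 4-week effect

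*Protocol article*

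**What the plan says.** **Timing of the SF-12.** The Outcomes and measurements section has patients in both groups complete it "in a French-validated version right after the consultation, and again, 4 weeks after the consultation". The abstract's Methods paragraph agrees: "scoring filled in by the patient immediately after the consultation and 4 weeks later". The place of the first form is also given: "The SF-12 questionnaire right after the consultation will be available in the waiting room". No earlier SF-12 is described anywhere in the text.

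**When the intervention reaches the patient.** GPs in the intervention group are trained beforehand and use the strategies in the visit. The first one listed in the Intervention section is "Being particularly receptive to the patient throughout the consultation".

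**Enrolment.** Under Patient inclusion criteria: "The GPs will inform the patient of the study after knowing the reason for the encounter, at the beginning of the consultation". Written consent follows the explanation.

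**Outcome and analysis.** Under Outcome: "The secondary outcome relates to the variation in the quality of life of patients after they have addressed the topic of PE". Under Statistical methods, the randomised groups are compared on the SF-12 "using an analysis of covariance for correlated data with the baseline score as a covariate".

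**The concern.** A baseline covariate in a randomised comparison is safe because allocation cannot have changed it. Here the covariate is recorded once the consultation is over, when the intervention has already been delivered to that patient. If the consultation shifts how patients answer the SF-12 and does so differently by arm, adjusting for that score distorts the estimated effect on 4-week quality of life.

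A simple change score from the first to the second form has the same weakness to a greater degree, because it subtracts the whole immediate shift.

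This is not a detail that an analysis plan could settle later. The article fixes both the timing and the covariate, and no later document can supply a pre-consultation score that was never collected. At stake is the only secondary outcome named in the Outcome section.

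**Working it through.** **1. Which score can be the baseline?** The text has two SF-12 scores. One is the 4-week outcome. The other is the form completed after the consultation, so it must be the covariate. The participant timeline and the schedule of procedures are figures that could not be read, but the abstract and the Outcomes and measurements section agree with each other.

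**2. What the ANCOVA estimates.** Let
- d4 = between-arm effect on the 4-week score,
- d0 = between-arm effect already present in the post-consultation score,
- b = within-arm slope of the 4-week score on the post-consultation score.

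The adjusted difference is the difference in 4-week means minus b times the difference in covariate means. With arms alike at entry, its expectation is d4 − b × d0. Writing d0 = f × d4, the share of d4 recovered is 1 − b × f.

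**3. Illustration.** The documents give no SF-12 effect, standard deviation, correlation or immediate shift, so b and f are assumptions.

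| f | b = 0.5 | b = 0.6 | b = 0.7 |
|---|---|---|---|
| 0 | 100% | 100% | 100% |
| 0.25 | 87.5% | 85% | 82.5% |
| 0.5 | 75% | 70% | 65% |
| 1 | 50% | 40% | 30% |

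For example, 1 − 0.6 × 0.5 = 0.70. With opposite signs, f = −0.5 and b = 0.6 give 1 + 0.30 = 1.30, an inflation of 30%.

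**4. Check by simulation.** Assumptions: 40 GPs with 15 patients each, ICC 0.05, SD 10, true 4-week effect 3 points, immediate effect 2 points, 400 replicates per setting. The shared GP effect makes the slope 0.95 × correlation + 0.05, that is 0.525, 0.62 and 0.715.

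| Correlation | Expected, 3 − 2 × slope | ANCOVA on post-consultation score | ANCOVA on pre-consultation score | Change score |
|---|---|---|---|---|
| 0.5 | 1.95 | 1.93 | 3.00 | 0.97 |
| 0.6 | 1.76 | 1.72 | 2.94 | 0.98 |
| 0.7 | 1.57 | 1.56 | 2.98 | 1.04 |

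The formula and the simulation agree. With no immediate effect, the post-consultation ANCOVA returned 3.05, 3.01 and 3.04, so nothing is lost. The change score keeps only about 3 − 2 = 1 point, so it is no remedy.

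**The case against.** **The intended quantity may be change after the topic was raised.** The abstract and the Outcome section speak of variation in quality of life after PE has been addressed, and the two measurement times fit that wording. This stands as a reason to state the target. It does not rescue the planned model: a between-arm ANCOVA on a post-exposure score does not estimate the intervention's effect on 4-week quality of life, and the score is still not a baseline.

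**The mechanism is assumed.** The SF-12 is a generic scale, and nothing in the documents shows that it shifts within minutes of a consultation. This stands. A reader might infer that the plan does adjust away part of the effect, or that the error is necessarily toward no effect. The documents support neither: the distortion may be zero and its direction depends on signs that are not known.

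**The absolute size may be small.** The sample size section plans for PE being raised by 5% against 20% of patients, a difference of 15 percentage points. If the effect runs only through raising PE, an assumed immediate gain of 3 points in each additional patient gives d0 = 0.15 × 3 = 0.45, and 0.6 × 0.45 = 0.27 points are removed. A 3-point arm effect, as in the simulation, would need 3 / 0.15 = 20 points per additional patient, or 2 SD at the assumed SD of 10. This is a fair caution about absolute size. The relative loss, 1 − b × f, is unchanged, and the dilution weakens if the strategies also affect patients who do not raise PE.

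**Leaving out the first score has its own cost.** Patients are enrolled by their GP after allocation, and the intervention GPs are not blinded, so the arms may differ at entry. A model without the first SF-12 gives up some control of that imbalance. This stands, and it is why neither model should be shown alone. The post-consultation score cannot itself separate an entry difference from an early effect.

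**Conclusion.** The concern holds in a conditional form. The SF-12 covariate is measured after exposure and allocation can affect it, so the planned ANCOVA targets d4 − b × d0. It understates the 4-week effect if the immediate and 4-week shifts share a sign, overstates it if they are opposite, and carries no bias from this source if there is no immediate shift.

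The recovery figures of 85%, 70% and 40% rest on an assumed slope of 0.6 and assumed immediate shifts. They must not be read as estimates of what this trial will lose. The matter is confined to the SF-12 secondary outcome and gives no ground to doubt the primary outcome, its model or the sample size. The change is worth making because it is cheap and the problem cannot be repaired once all first forms have been collected after the visit.

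**What to change.** **Patients still to be enrolled.** Have the first SF-12 completed directly after consent is signed and before the consultation continues, and keep the ANCOVA on that score. Consent already comes at the start of the visit, the Trial status section says recruitment was not complete at submission, and the Monitoring section lets the Steering Committee agree protocol changes.

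**Patients already enrolled.**
- Stop calling the first score baseline, and report it by arm as an outcome.
- Present the 4-week SF-12 comparison from a mixed model with a GP random effect, adjusted only for pre-consultation variables: region, GP gender, patient age and reason for encounter.
- Show the planned ANCOVA beside it, described as an effect conditional on the immediate post-consultation score.
- Do not replace the ANCOVA by a change score.

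**Costs.** The visit is briefly interrupted, which matters because the Background names lack of time as the main obstacle for GPs, and the form must be to hand in the consulting room. Even then the patient will have had the study explained by a GP who may be trained. There will be two SF-12 timings, to be analysed separately. The model without the first score has wider intervals and less control of entry imbalance, so both analyses should be shown.
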